#### Secondary Outcomes

##### NSSI Features

The Nonsuicidal Self-Injury Disorder Scale [36] is a self-report measure designed to assess the proposed criteria for NSSI disorder (as stated in the *Diagnostic and Statistical Manual of Mental Disorders*, *Fifth Edition*) [37]. The Spanish version of the scale shows good internal reliability (Cronbach α=0.88) [36].

##### Emotion Regulation

The brief version of the DERS-18 is the shortened form of the original DERS [22]. The Spanish translation of this scale is being used. The DERS-18 preserves the original 6-subscale structure assessing key domains of ER difficulties, including a lack of emotional awareness, a lack of emotional clarity, nonacceptance of emotions, inability to engage in goal-directed behavior when feeling emotional, engagement in impulsive behavior when feeling emotional, and inability to access ER strategies. The scale demonstrates strong internal consistency, with a total score of Cronbach α=0.91 [38].

The Brief Experiential Avoidance Questionnaire is a 15-item measure assessing an individual’s tendency to avoid or escape from unwanted internal experiences such as uncomfortable emotions, thoughts, memories, or sensations [39]. The Spanish version is being used and shows good internal consistency (Cronbach α=0.82) [39].

##### Symptoms

The Depression Anxiety Stress Scales–21 is a self-report measure that evaluates the frequency and severity of 21 negative emotional symptoms experienced over the past week, organized into 3 subscales: depression, anxiety, and stress. The Spanish version of the scale has shown moderate to good internal consistency, with Cronbach α coefficients of 0.84 for depression, 0.70 for anxiety, and 0.82 for stress [40].

The Borderline Symptom List–23 [41] assesses BPD symptom severity. Participants rate each item on a 5-point Likert scale from 0 (not at all) to 4 (very strong). The Spanish version of the scale is being used, which has high reliability (Cronbach α=0.949) [42].

##### Social Support

Perceived social support is being measured using the Multidimensional Scale of Perceived Social Support [43]. In this study, the validated Spanish version of this scale is being used, which shows good internal reliability (Cronbach α=0.88) [44]. A high score indicates greater social support, and the response format ranges from 1 (completely disagree) to 7 (completely agree).

##### Process Measures

The Dialectical Thinking Scale [45] is a validated 5-item measure assessing dialectical thinking. It consists of a 2-factor structure: “Both Sides,” which reflects the ability to acknowledge and accept opposing viewpoints as equally valid (thereby promoting cognitive flexibility and minimizing polarized thinking) and “Both Sides in Me,” which captures the capacity to incorporate and accept internal contradictions. This scale demonstrates strong psychometric properties, with high internal consistency (Cronbach α=0.81) and sound test-retest reliability (intraclass correlation coefficient=0.82 for “Both Sides” and 0.64 for “Both Sides in Me”).

The Delusion of Me is a 24-item questionnaire assessing a latent construct proposed to unify 3 core mindfulness-related processes: acceptance, decentering, and nonattachment. The general factor showed good reliability, with a hierarchical omega (ωh) of 0.81, indicating that most of the reliable variance in the composite score is attributable to the general construct, rather than to specific subcomponents [46]. Participants rate each item on a 5-point Likert scale ranging from 1 (not at all true or rarely true) to 5 (always or very frequently true).

##### Well-Being

The Pemberton Happiness Index [47] integrates hedonic and eudaimonic aspects of well-being. The Spanish version of the index is being used, which shows high internal consistency (Cronbach α=0.91).

The Positive and Negative Affect Schedule is a 20-item self-report measure assessing positive affect (ie, interested, satisfied, and excited) and negative affect (ie, anxious, guilty, and aggressive). Participants rate each item on a scale ranging from 1 (very slightly or not at all) to 5 (extremely), indicating the extent to which each adjective describes their current mood at the time of completing the questionnaire. The result is the sum of the values. This scale is useful to measure emotional fluctuations throughout a specific period, and a Spanish adaptation is being used [48].

##### User Experience

To evaluate user experience with the app, participants complete the System Usability Scale, a 10-item tool with strong reliability for assessing perceived usability of digital technologies. Items are rated from 1 (strongly disagree) to 5 (strongly agree). The SUS score can be interpreted with a qualitative scale ranging from “worst imaginable” to “best imaginable” usability [49].

##### Daily Assessment

EMAs delivered via the app collect real-time data throughout the intervention phase corresponding to the 5 different EMI domains as previously described in Table 1.

### Randomization and Procedure

Figure 3 depicts the evaluation, randomization, and allocation of participants to intervention 1 or intervention 2 between participant groups. Following screening, eligible participants in the NSSI clinical and NSSI subclinical groups are being randomized to either intervention 1 or intervention 2 using an adaptive randomization procedure stratified by age (14-16, 17-19, and 20-24 years) and sex. This approach ensures a balanced distribution across intervention arms. Each treatment group will include 120 participants, divided evenly between the clinical and subclinical groups. In addition, both intervention conditions continue to receive treatment as usual in the NSSI clinical group, which may include psychological or pharmacological care within a public health unit.

Participants receive access to either version of the app, which has been developed for both Android and iOS platforms. To use the app, the user obtains an access code from the researcher, and the app remains active for 6 weeks.

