### Sample Size Calculation

Power analyses conducted using G*Power (version 3.1) indicated that, to detect a medium effect size (Cohen *f*=0.27) with 90% power and a significance level of .05, 100 participants per group are required. Allowing for up to 20% attrition, 120 participants will be recruited per intervention arm, resulting in a total NSSI sample of 240 participants.

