### Statistical Analysis

Primary analyses will be conducted using linear mixed-effects models to evaluate the impact of the intervention on both momentary and self-report outcomes. Time (T0, T1, T2, and T3) will be included as a within-subject factor, while intervention (intervention 1 vs intervention 2) and group (clinical vs subclinical) will be modeled as between-subject factors. Random intercepts for participants and random slopes for time will be specified. Secondary analyses will explore potential moderators and mediators of treatment response, including app engagement, baseline severity, and demographic variables. Missing data will be addressed using maximum likelihood estimation under the assumption that data are missing at random.

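### Allocation is balanced on age band and sex, but the primary mixed model names neither; if they predict change from T0, its standard error is somewhat too wide

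*Protocol article*

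**What the plan says.** Under Randomization and Procedure, the protocol article randomizes eligible participants in the clinical and subclinical groups "using an adaptive randomization procedure stratified by age (14-16, 17-19, and 20-24 years) and sex", and gives the purpose: "This approach ensures a balanced distribution across intervention arms".

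Under Statistical Analysis, the primary model is a linear mixed model with T0 to T3 as the levels of a within-person time factor. For the terms that differ between participants, the article states that "intervention (intervention 1 vs intervention 2) and group (clinical vs subclinical) will be modeled as between-subject factors". On the random part of the model it adds: "Random intercepts for participants and random slopes for time will be specified". Age and sex are not named. The only place for them is the sentence on secondary work: "Secondary analyses will explore potential moderators and mediators of treatment response, including app engagement, baseline severity, and demographic variables".

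The article says nothing on how strongly age or sex is related to NSSI frequency or to its change.

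**The concern.** Balancing the arms on a factor removes that factor's chance contribution to the difference between arms. A model without the factor does not know this: it leaves the factor's variance in the residual and prices in an imbalance that the design has prevented. The reported standard error then exceeds the true sampling variability, confidence intervals are too wide, and the test rejects a true null less often than its nominal 5%.

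What is at stake is precision and a little power. The estimate is not biased, and the error is on the conservative side.

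**Working it through.** **Inputs from the article.** Two arms of 120, half clinical and half subclinical; three age bands and sex, which is six strata if sex is binary; T0 to T3 as response levels; participant intercepts and time slopes; a sample size set "to detect a medium effect size (Cohen *f*=0.27) with 90% power" at a significance level of .05, with 100 evaluable per group.

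**Assumed, because the article gives no value.** R², the share of the variance of the analysed contrast that age band and sex explain (0 to 0.20); near-perfect balance on those factors; a within-person correlation of 0.5 in the simulation.

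**The plan's own figure.** The article has no figure on this point. Its sample size reproduces as a four-cell omnibus F test (3 numerator degrees of freedom, f = 0.27), which needs 199 in total and has power 0.903 at 200. Nothing below changes it.

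**Step 1: closed form.** With balanced, omitted factors:

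- model SE / true SE = 1/√(1 − R²)
- SE reduction from adjusting = 1 − √(1 − R²)
- true type I error = 2 × [1 − Φ(1.96/√(1 − R²))]

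For R² = 0.10: √0.90 = 0.949, so the ratio is 1.054, the reduction is 5.1%, and 1.96/0.949 = 2.066 gives a type I error of 0.039.

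For power, take 100 per arm and the standardized difference that has 90% power when R² = 0: d = (1.960 + 1.282) × √(2/100) = 0.458, so d/SE = 3.242. Power without adjustment is Φ((3.242 − 1.960)/√(1 − R²)); with adjustment it is Φ(3.242/√(1 − R²) − 1.960).

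| R² (assumed) | model SE / true SE | SE reduction | type I error | power without | power with |
|---|---|---|---|---|---|
| 0 | 1.000 | 0% | 5.0% | 0.900 | 0.900 |
| 0.02 | 1.010 | 1.0% | 4.8% | 0.902 | 0.906 |
| 0.05 | 1.026 | 2.5% | 4.4% | 0.906 | 0.914 |
| 0.10 | 1.054 | 5.1% | 3.9% | 0.912 | 0.927 |
| 0.20 | 1.118 | 10.6% | 2.8% | 0.924 | 0.952 |

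**Step 2: which contrast R² refers to.** The hypothesis is a greater reduction, and T0 is a response level, so the effect of interest is intervention by time: in essence, the difference between arms in change from T0. A stable difference in level between, say, younger and older participants is in both T0 and follow-up and cancels. Only an association with change remains.

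This was simulated with 6,000 trials per scenario, n = 240 and permuted blocks within clinical group and six strata. The Monte Carlo error on type I error is about 0.003. For the change contrast without stratum terms:

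| level R² | change R² | model SE / empirical SD | type I error |
|---|---|---|---|
| 0 | 0 | 1.00 | 0.047 |
| 0.10 | 0 | 1.01 | 0.048 |
| 0.20 | 0 | 1.01 | 0.048 |
| 0.10 | 0.05 | 1.03 | 0.042 |
| 0.10 | 0.10 | 1.05 | 0.043 |
| 0.20 | 0.20 | 1.10 | 0.032 |

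With stratum terms in the analysis of change, the last three ratios become 1.00, 1.00 and 0.99, with type I error 0.048, 0.053 and 0.052. For a comparison of post scores alone, level does matter: at level R² of 0.10 and 0.20 the ratio without stratum terms is 1.07 and 1.10.

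**Step 3: which terms recover the loss.** A main effect of age band or sex adds the same constant at every time point, so it drops out of a within-person change and leaves the intervention-by-time SE essentially as it was. A small run of the stated model (four times, random intercept and slope, 12 data sets per scenario) agrees: stratum main effects changed the SE by a factor of 1.000 to 1.004, while stratum-by-time terms gave 0.98 and 0.94 where the strata predicted change.

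**The case against.** The best defence has three parts. First, a journal article condenses the full protocol, and its Statistical Analysis section does not rule out further covariates. That stands as a caution. However, the article does name the between-subject factors and does place demographic variables in secondary analyses, so a reader would take the primary model to be without them.

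Second, with T0 in the response, level differences cancel, and nothing in the article shows that age or sex predicts change. This stands too, and it is why the point is conditional. A link with change is still plausible: under Primary Outcome, the ISAS covers lifetime frequency at T0 and the last month at follow-up. A lifetime count has longer to accumulate in a 24-year-old than in a 14-year-old, so age may well predict the difference between the two.

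Third, planned power is kept. This stands: power without adjustment is 0.906 to 0.924 in the closed form for R² of 0.05 to 0.20. What is forgone is 0.8 to 2.8 percentage points.

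Two stronger readings are tempting. A reader might infer that the standard errors are too wide as a matter of fact; with no association with the contrast they are correct. A reader might also infer that the even clinical split ("Each treatment group will include 120 participants, divided evenly between the clinical and subclinical groups") is unprotected because clinical status is not listed beside age and sex. The text describes randomizing participants in the clinical and in the subclinical group, each recruited to 120, which most naturally means allocation within each group. The flowchart that would settle it is not shown. The documents do not support an imbalance claim.

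**Conclusion.** The point holds in conditional form. Two factors that govern allocation are not among the terms named for the primary model. To the extent that they predict change from T0, the model-based SE is too wide and the test mildly conservative: type I error of about 4.4%, 3.9% or 2.8% at R² of 5%, 10% or 20%. At R² of zero there is no loss. These sizes rest on assumed R² values and on near-perfect balance on age band and sex. This is a modest, inexpensive gain in efficiency, worth making because the article itself warns that the study may be underpowered for small-to-moderate effects.

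**What to change.** Before outcome data are analysed by arm, state in the analysis plan that the primary model includes age band (three levels) and sex as fixed effects, together with their interactions with time. Main effects alone are enough only if the model is recast as a baseline-adjusted comparison of post-baseline scores. Do not add baseline NSSI as a covariate while T0 remains a response level; use one approach or the other.

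The cost is wording, with data the allocation already requires. Main effects take 2 + 1 = 3 degrees of freedom. Interactions take 3 × 3 = 9 more coefficients if time has four levels, or 3 more if time is linear, in a trial of 240. Randomization and sample size need no change on this account.

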**Figure 3 figure3:**
[figure not shown]
Study flowchart. TAU: treatment as usual.

### Sample Size Calculation

Power analyses conducted using G*Power (version 3.1) indicated that, to detect a medium effect size (Cohen *f*=0.27) with 90% power and a significance level of .05, 100 participants per group are required. Allowing for up to 20% attrition, 120 participants will be recruited per intervention arm, resulting in a total NSSI sample of 240 participants.

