Expected results may inform the development of personalized digital care pathways by identifying both stable (eg, personality traits) and dynamic (eg, emotional fluctuations) predictors of intervention response. This approach aligns with contemporary calls for precision mental health frameworks and could help segment users into subgroups most likely to benefit from specific components or delivery modes.

However, some limitations are anticipated. As a pilot trial, the study may be underpowered to detect small-to-moderate clinical effects and may lack a long-term follow-up. Reliance on self-report and EMA data, although informative, introduces potential for missing data and response biases. App engagement may also vary significantly across users, and understanding dropout or nonuse patterns will be critical for informing future iterations. Additionally, although the intervention is informed by established therapeutic models, its brevity and digital delivery format may limit its scope compared with comprehensive face-to-face treatment.

Despite these limitations, this trial represents a meaningful step toward a scalable and accessible intervention for people with NSSI. It leverages real-time data to adapt support to user needs, draws from stakeholder expertise, and targets an underserved but highly affected population. Findings from this feasibility phase will inform iterative improvements to Kalmer and lay the groundwork for future large-scale evaluations of its clinical efficacy and cost-effectiveness.

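### With 20% attrition, 120 per arm leaves 96 evaluable, not the 100 required; and the unnamed test that reproduces 100 per arm is not the two-arm contrast in the hypothesis

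*Protocol article*

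**What the plan says.** The Sample Size Calculation section of the protocol article reports a G*Power 3.1 calculation "to detect a medium effect size (Cohen *f*=0.27" and concludes that "with 90% power and a significance level of .05, 100 participants per group are required". It continues: "Allowing for up to 20% attrition, 120 participants will be recruited per intervention arm", "resulting in a total NSSI sample of 240 participants". It does not name the test family, the number of groups or the numerator degrees of freedom.

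Three other places bear on the point:

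- The Objective in the Abstract states a two-arm hypothesis: NSSI frequency falls more with the specific app than with the nonspecific one, at end of treatment and at follow-up.
- Randomization and Procedure splits each arm of 120 evenly into clinical and subclinical participants, which gives four cells of 60. Statistical Analysis enters intervention and clinical status as separate between-subject factors in a linear mixed model over T0 to T3.
- The Discussion warns: "As a pilot trial, the study may be underpowered to detect small-to-moderate clinical effects".

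**The concern.** The section sets a required evaluable number and an attrition allowance, and the recruitment target does not meet the first once the second is applied. This can be seen within two sentences and needs no assumption about the test.

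Separately, a reader will take the 90% to be the power for comparing the two apps. If it belongs to an omnibus test over four cells, it answers another question, because such a test can reach significance through a difference between clinical and subclinical participants alone. What is at stake is interpretation: after a null result, readers need to know which effect between the arms the trial was able to detect.

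**Working it through.** **Inputs.** From Sample Size Calculation: f = 0.27, power 90%, alpha .05, 100 per group, attrition up to 20%, 120 per arm, 240 in total. From Randomization and Procedure: two equal arms, each split evenly by clinical status. Not stated: the test, its numerator df, and the number of groups.

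**Formula.** Power of the fixed-effects F test = P(F′ > F_crit), where F′ is noncentral F with df1, df2 = N − k and noncentrality λ = f²N.

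**1. Reproducing the plan's figure.** Take k = 4 cells (two arms × clinical/subclinical) and df1 = 3.

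- N = 200: λ = 0.27² × 200 = 14.58; power 90.3%.
- The smallest N reaching 90% is 199, which rounds to 200 with equal cells: 50 per cell, 100 per arm.

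So 100 per arm reproduces. Other variants did not give 200. A 2-df effect needs 177 to 180. Repeated-measures versions with 2 to 4 time points and assumed correlations of 0.3 to 0.8 need at most 179.

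**2. The two-arm contrast at the same f.** Take df1 = 1.

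- N = 147 is the smallest that reaches 90%; with equal arms this is 148, or 74 per arm (λ = 10.79, power 90.4%). Keeping all four cells and testing a 1-df effect also gives 148.
- N = 200: power 96.7%.

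**3. Attrition.**

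- Evaluable at 20% loss: 120 × 0.80 = 96 per arm, 192 in total.
- Recruits needed to keep 100: 100/0.80 = 125 per arm, 250 in total.
- Loss at which 120 still leaves 100: 1 − 100/120 = 16.7%.
- 100 × 1.2 = 120, which shows how the figure probably arose.

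**4. Consequence at N = 192** (λ = 0.27² × 192 = 14.00 for f = 0.27).

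| Test | Power at f = 0.27 | f detectable with 90% power |
|---|---|---|
| Four cells, 3 df | 88.9% | 0.275 |
| Two arms, 1 df | 96.1% | 0.235 (d = 2f = 0.47) |

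**5. Smaller effects, two-arm test, N = 192** (f = d/2).

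| d | Power |
|---|---|
| 0.20 | 28% |
| 0.30 | 54% |
| 0.40 | 79% |

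All two-arm figures treat the comparison as two group means at one time point. The mixed model's power also depends on variances and correlations that the article does not give.

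**The case against.** The strongest defence is that 100 per arm is not a mistake. The section does not claim a two-arm, 1-df test, and its figure follows exactly from the stated inputs in a four-cell layout that matches the design. That stands. A reader might infer that the power statement is wrong twice and that the correct number is 74 rather than 100. The article does not support this: 74 is the answer for a test the section never says it used. What remains is that the 90% is not tied to the hypothesis it appears to serve. Even the four-cell explanation is an inference from a numerical match.

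A reader might also infer that the Discussion's caveat about being underpowered conflicts with a 90% power claim and should go. It does not conflict. The calculation targets a medium effect and the caveat concerns smaller ones, for which the two-arm power at 192 is 28% at d = 0.20 and 54% at d = 0.30.

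Nor can one say that the planned analysis has more power than stated. The two-group figure is only an approximation to a mixed model over four time points, and the hypothesis covers follow-up as well as end of treatment.

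Finally, the attrition slip is small, and maximum likelihood under missing at random lets participants with partial follow-up contribute, so 96 is a cautious count. That limits the consequence, but it does not make 120 with 20% loss equal to 100.

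**Conclusion.** The attrition error holds without qualification. At the stated 20%, 120 per arm leaves 96, four short of the stated requirement; 5 more recruits per arm (10 in total) would have been needed to meet it. Under the test that reproduces the plan, power falls from 90.3% to 88.9%, about one point.

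The second part holds as a mismatch, not as an arithmetic error. The test behind f = 0.27 is unnamed, and the calculation that reproduces 100 per arm is a 3-df omnibus test, not the two-arm contrast in the hypothesis. For that contrast, 74 per arm would suffice at f = 0.27, so the mismatch causes no shortfall. This rests on two assumptions: that the four-cell test was the one run, and that a single-timepoint comparison of two means is a fair guide to the mixed model.

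Severity is minor. The recruitment target is not endangered.

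**What to change.** Keep 240 and change the wording of Sample Size Calculation:

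1. State that 120 per arm leaves 96 evaluable per arm (192 in total) at 20% attrition, or that 100 evaluable per arm allows for 16.7% attrition.
2. Name the test, the number of groups and the numerator df behind f = 0.27.
3. Add the power for the two-arm contrast, for example: with 96 evaluable per arm and two-sided alpha .05, about 96% for f = 0.27 and 90% for f = 0.235 (d = 0.47). Label it as a simple single-timepoint two-group approximation to the planned mixed model.

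Leave the Discussion's caveat on small-to-moderate effects as it is. The cost is a few sentences and no additional participants. The Results section reports 145 of the planned 240 with baseline assessments in January 2026 and recruitment still open, so on that status the text can be corrected before results are known.
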